### 2.6. Participation Timeline

The expected duration of the study is three years following ethical approval by the local ethical review committee. As a first step, eligibility criteria will be analyzed at patients’ admission to the catheterization laboratory. Patients will be enrolled if all inclusion criteria will be fulfilled. During primary PCI procedure, HRV will be continuously monitored using a wearable device, which will be further analyzed offline using Kubios software. Additionally, at the index procedure demographic data, time to primary PCI in relation to chest pain onset; data regarding comorbidities and cardiovascular risk factors; and specified clinical, biological, and echocardiographic parameters will be collected.

During the hospital stay, patients will be re-evaluated echocardiographically and pre-discharge LVEF will be recorded. All outcomes of interest will be reported at this first time point in order to analyze a possible correlation between previously measured HRV parameters and short-term adverse events.

At 1 month and at 12 months after the index event, HRV will be re-assessed. In addition, in these time frames, clinical and echocardiographic data will be collected. Primary and secondary outcomes will be reported and an eventual correlation with HRV measured during primary PCI, as well as after 1 month and 12 months, will be analyzed.

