## Abstract

Background: Heart rate variability (HRV) could have independent and critical prognostic values in patients admitted for ST segment elevation myocardial infarction (STEMI). There are limited data in the literature regarding HRV assessment in STEMI setting. Thus, we aim to investigate the potential correlations between HRV and adverse outcomes in a contemporary cohort of patients presenting with STEMI undergoing primary percutaneous coronary intervention (PCI). Methods: We will perform a prospective, observational cohort study in a single healthcare center. Adult patients aged ≥18 years presenting with STEMI in sinus rhythm will be enrolled for primary PCI within 12 h from symptoms onset. Time domain, frequency domain, and nonlinear HRV parameters will be measured using a medically approved wrist-wearable device for 5 min segments during myocardial revascularization by primary PCI. Additional HRV measurements will be performed one and six months from the index event. The primary composite outcome will include all-cause mortality and major adverse cardiovascular events (during the hospital stay, one month, and one year following admission). Several secondary outcomes will be analyzed: individual components of the primary composite outcome, target lesion revascularization, hospitalizations for heart failure, ventricular arrhythmias, left ventricular ejection fraction, and left ventricular diastolic function. Conclusions: Our study will enlighten the reliability and usefulness of HRV evaluation as a prognostic marker in contemporary patients with STEMI. The potential validation of HRV as a risk marker for adverse outcomes following STEMI will ensure a background for including HRV parameters in future risk scores and guidelines.

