### 2.3. HRV Parameters Measured

We will measure HRV parameters recommended by the ESC and the North American Society of Pacing and Electrophysiology guidelines [7]:

(1)Time domain parameters: standard deviation of all NN intervals (SDNN), HRV triangular index, the standard deviation of the average NN interval over short time divisions (SDANN), and the square root of the mean squared differences of consecutive NN intervals (RMSSD);(2)Frequency domain parameters: low-frequency power (LF), high-frequency power (HF), and LF/HF ratio.

Additionally, some nonlinear HRV parameters will be evaluated, such as SD1, SD2, SD2/SD1, approximate entropy, and sample entropy.

HRV will be measured in addition to medical and interventional therapy for myocardial infarction according to the latest ESC guidelines focused on STEMI [2]. HRV will be assessed using a medically approved wrist-wearable device (E4 wristband from Empatica, CE certified) for 5 min segments during myocardial revascularization by primary PCI (before and after revascularization). The E4 device will be placed on the non-dominant hand, with the case tightener on the top of the wrist. The validity of HRV measurement using an Empatica E4 wristband was previously confirmed in a clinical study [13]. Raw data regarding heart rate and HRV (interbeat interval data) will be extracted from the wristband and further analyzed using Kubios software. Among available E4 wristband sensors, photoplethysmography will be used to derive interbeat interval data from blood volume pulse analysis. The blood volume pulse signal has a sampling rate of 64 Hz (resolution 1/64 s) as specified by the manufacturer. All HRV parameters of interest (including frequency domain and nonlinear parameters) will be automatically calculated using Kubios software [18]. Moreover, eventual artifacts in raw data collection will be corrected using a very low threshold algorithm (0.45 s) in Kubios to avoid significant HRV parameters deformation. Additional HRV measurements will be performed after the index event (at one and six months).

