### 2.5. Outcomes and Follow-Up

The primary composite outcome will include all-cause mortality and major adverse cardiovascular events (MACE). MACE will include cardiac mortality, fatal and non-fatal myocardial infarction, unplanned target vessel revascularization (TVR), and stroke (ischemic or hemorrhagic).

In addition, several secondary outcomes will be analyzed: (a) all-cause and cardiac mortality; (b) fatal and non-fatal myocardial infarction; (c) unplanned target vessel revascularization; (d) target lesion revascularization (TLR); (e) stroke; (f) hospitalizations for heart failure; (g) ventricular arrhythmias; (h) LVEF and left ventricular diastolic function. Moreover, the primary composite outcome will be evaluated in a high-risk subgroup of patients, such as elderly patients or those with diabetes mellitus/chronic kidney disease.

TVR will be defined as new stenosis requiring PCI or CABG in another part of the coronary artery treated at the index event. TLR will include unplanned PCI or CABG for the same lesion revascularized during primary PCI. LVEF will be measured using two-dimensional transthoracic echocardiography (Simpson methods). At least E/A or E/e prime ratios will be calculated for left ventricular diastolic function. Ventricular arrhythmias will be defined as ventricular fibrillation or sustained ventricular tachycardia documented at electrocardiographic monitoring. The primary composite outcome and secondary outcomes will be evaluated during the hospital stay, at 1 month and 1 year following admission for STEMI. All data regarding the outcomes will be collected from secure medical records.

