### 2.7. Statistical Analysis

SPSS statistical software version 26.0 will be used (IBM SPSS Statistics, New York, NY, USA). Descriptive statistics will be applied to characterize enrolled patients. Normally distributed data will be represented as mean and standard deviation, while non-normal distributed data will be displayed as median and Inter Quartile Range (IQR). Also, relevant graphics will be used when possible. 

When appropriate, data will be analyzed using parametric (Student’s *t*-test) and non-parametric tests (Mann–Whitney–Wilcoxon). In addition, for statistical hypothesis testing, Student’s *t*-test will be applied in case of continuous variables, while categorical variables will be compared using the chi-square test. Missing data will be handled using a multiple imputation approach.

Odds ratio (OR), corresponding 95% confidence intervals, and p-values will be calculated for each variable related to investigated outcomes. A *p*-value < 0.05 will be considered statistically significant. Univariate logistic regression models will reveal statistically significant variables associated with pre-specified outcomes. Afterward, variables documented as statistically significant in univariate logistic regression models will be included in multivariate analysis. Moreover, the prediction accuracy of time and frequency domain HRV parameters for primary and secondary outcomes will be evaluated using the Receiver Operator Characteristics (ROC) curve. The sensibility, specificity, and c-statistic of individual HRV parameters will be calculated. Additionally, the Kaplan–Meier survival curve will be used to analyze time to event variables.

In addition, the role of HRV parameters for adverse outcomes prediction will be analyzed in three subgroups of high-risk patients, including patients with chronic kidney disease, diabetes mellitus, and elderly participants.

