**Assessments**					
Clinical data		X	X	X	X
Primary composite outcome			X	X	X
Secondary outcomes			X	X	X

ECG = electrocardiography; HRV = heart rate variability; PCI = percutaneous coronary intervention.

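### HRV measured at 12 months cannot predict clinical outcomes that end at 1 year, and 1-month HRV is not restricted to later events

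*Protocol article*

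**What the plan says.** Section 2.6 sets the follow-up measurements: "At 1 month and at 12 months after the index event, HRV will be re-assessed". It then says that outcomes will be reported and that "an eventual correlation with HRV measured during primary PCI, as well as after 1 month and 12 months, will be analyzed". For in-hospital events the same section speaks only of HRV already measured; the follow-up sentence carries no such limit.

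Section 2.5 fixes the outcome times: they "will be evaluated during the hospital stay, at 1 month and 1 year following admission for STEMI". Table 1 agrees. Its "Primary composite outcome" row is marked for the hospital stay, 1 month and 12 months, and its HRV row for baseline, 1 month and 12 months. The primary composite contains all-cause death.

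The Introduction states a prognostic aim. Section 2.7 specifies odds ratios from logistic regression and ROC analysis of how well HRV predicts the primary and secondary outcomes. Its rule on missing values is one sentence: "Missing data will be handled using a multiple imputation approach".

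The later HRV visit is not consistent. The Abstract says "Additional HRV measurements will be performed one and six months from the index event", and section 2.3 agrees with it. Section 2.6 and Table 1 put that visit at 12 months.

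**The concern.** A prognostic marker has to be measured before the events it is tested against. HRV recorded at the last outcome visit comes after all of them. Reinfarction, stroke, repeat revascularisation or a heart-failure admission could each alter HRV afterwards. An association with HRV measured later may then run from event to HRV, yet be reported as an odds ratio or c-statistic for prediction.

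Death makes the problem sharper. A patient who dies has no later HRV, so the most important component of the primary outcome drops out of the observed data. The imputation sentence sets no boundary that would stop values being generated for those patients.

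**Working it through.** The article gives no event rate, effect size or derivation for its 200 patients, so there is no figure of the plan's own to reproduce. The check is the time order, followed by an illustrative simulation.

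**Step 1: time order.** HRV times are from section 2.6, with six months from the Abstract and section 2.3. Outcome times are from section 2.5. I take the 1-year outcome as cumulative from admission, which the text implies but does not state.

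| HRV measured at | In-hospital events | Events to 1 month | Events to 1 year |
|---|---|---|---|
| Index PCI | follow HRV | follow HRV | follow HRV |
| 1 month | precede HRV | precede HRV | mixed: months 1–12 follow |
| 12 months | precede HRV | precede HRV | precede HRV |
| (6 months) | precede HRV | precede HRV | mixed: months 6–12 follow |

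On the section 2.6 schedule, 3 of the 9 pairings are in prognostic order, 1 is mixed and 5 are reversed. For 12-month HRV all three are reversed.

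**Step 2: mortality.** Patients dead by 12 months with an observed 12-month HRV: 0. An observed-data logistic model of 1-year death on 12-month HRV has no events and no estimable odds ratio. Any estimate would come entirely from imputed values.

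**Step 3: simulation with no prognostic effect.** Assumptions not in the documents:
- deaths and non-fatal events by 12 months of 5% and 5%, 5% and 10%, or 10% and 10%;
- half of events before month 1;
- correlation of baseline with later HRV of 0.6;
- a non-fatal event lowers later HRV by δ = 0, 0.3, 0.5 or 0.8 SD;
- death the only reason for missing HRV.

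From the document: N = 200 and α = 0.05 (taken as two-sided). There were 1000 datasets per scenario. Events are drawn independently of baseline HRV h₀ ~ N(0,1), and later HRV is

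h_t = 0.6·h₀ + √(1 − 0.6²)·ε − δ·1{non-fatal event before t} = 0.6·h₀ + 0.8·ε − δ·1{…}

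Each fit is logit P(event) = a + b·h, significant if |b|/SE > 1.96. Imputation, where used, has 10 draws conditional on baseline HRV and outcome.

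Percentage of datasets significant (range over the three event-rate settings):

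| Analysis | δ = 0 | δ = 0.3 | δ = 0.5 | δ = 0.8 |
|---|---|---|---|---|
| 12-month HRV, survivors | 3.3–4.6 | 15.7–23.8 | 35.0–55.7 | 65.0–90.7 |
| 12-month HRV, dead imputed | 3.4–4.8 | 16.5–26.5 | 39.3–62.6 | 70.8–92.3 |
| 1-month HRV, cumulative 1-year outcome | 4.2–4.7 | 6.1–8.5 | 8.0–15.9 | 16.8–31.4 |
| 1-month HRV, landmark | 4.1–5.2 | 4.4–5.2 | 4.0–5.2 | 4.3–5.5 |
| Index HRV | 3.7–5.7 | 3.6–6.2 | 4.0–4.3 | 4.7–5.3 |

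The Monte Carlo standard error at a true 5% is √(0.05 × 0.95/1000) = 0.7 percentage points.

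**Step 4: analytic check.** With unit-variance normal HRV shifted by δ, the log odds ratio per SD is −δ. So exp(−0.3) = 0.74, exp(−0.5) = 0.61 and exp(−0.8) = 0.45. The simulated medians among survivors were 0.72–0.74, 0.59–0.60 and 0.44–0.45.

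**Step 5: patients affected.** Under the assumed rates, deaths without 12-month HRV number 200 × 0.05 = 10 to 200 × 0.10 = 20.

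**The case against.** The strongest case on the other side has five parts.

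- **1-month HRV is a sound marker for later events.** This stands. A reader might infer that all follow-up HRV looks backwards, but outcomes run to 1 year and months 1 to 12 lie ahead of the 1-month visit. What is missing is the restriction to patients still at risk. An unseen analysis plan could supply that, and the 1-month inflation is much smaller than the 12-month one.
- **The article does not say that HRV is imputed for the dead.** This stands. A reader might infer it from the unqualified sentence in section 2.7, but the sentence names no variable and does not mention death. In the simulation imputation adds little for the composite; for mortality it would be decisive.
- **Section 2.6 speaks of correlation, and section 2.7 does not say which HRV measurement enters the ROC analysis.** True. But the stated aim is prognostic, and nothing keeps follow-up HRV out of the logistic and ROC analyses.
- **Some secondary outcomes are measured at the visit itself.** This stands. LVEF and diastolic function come from echocardiography at the same visits as HRV, and a cross-sectional correlation with them is coherent.
- **The simulation is nearly circular.** Largely fair. It puts in a post-event shift and reports the power to detect it. It shows how readily such a shift would pass as prediction with 200 patients, not that the shift exists.

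No analysis plan can make 12-month HRV precede outcomes that stop at 12 months. That part does not depend on anything left out of the article.

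**Conclusion.** The point holds in this form. On the schedule in section 2.6 and Table 1, 12-month HRV cannot be prognostic for any planned clinical event; this follows from the dates alone. HRV at 1 month is a valid predictor of events in months 1 to 12, but the plan also relates it to earlier events.

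The size of any bias depends on how far events change HRV, which the documents do not give. For an assumed drop of 0.3 to 0.8 SD, false significance is roughly 16–91% for 12-month HRV among survivors and 6–31% for 1-month HRV against the cumulative outcome. With no drop, both stay near 5%. Reverse causation is therefore a risk, not an established result.

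A reader might also infer that the study's main question is compromised. The documents do not support that: HRV recorded at the index procedure keeps its time order, and its error rate stayed near 5% throughout. If the later visit is in fact at six months, the second half of the year still lies ahead and the problem becomes that of the 1-month measurement.

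**What to change.** Amend sections 2.6 and 2.7 before analysis:

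1. Name index HRV as the exposure for the main prognostic analyses.
2. Relate 1-month HRV only to events after that visit, in patients alive and free of the outcome at the visit (landmark analysis).
3. For clinical events, report HRV measured at the end of follow-up descriptively and keep it out of odds-ratio and ROC prediction analyses. Its correlation with same-visit LVEF and diastolic function may stay, labelled cross-sectional.
4. State that HRV after death is undefined and that multiple imputation does not extend to it.
5. Reconcile the later HRV visit: six months in the Abstract and section 2.3, 12 months in section 2.6 and Table 1. If it is six months, apply the landmark rule there too.

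The cost is wording and a data cut by date; no new data are needed. The landmark analysis has fewer events. Under the assumed rates, 200 × 0.10 = 20 to 200 × 0.20 = 40 events by 12 months, with half before month 1, leave about 10 to 20. The correlation of clinical events with end-of-follow-up HRV ceases to be a prognostic result.

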### 2.7. Statistical Analysis

SPSS statistical software version 26.0 will be used (IBM SPSS Statistics, New York, NY, USA). Descriptive statistics will be applied to characterize enrolled patients. Normally distributed data will be represented as mean and standard deviation, while non-normal distributed data will be displayed as median and Inter Quartile Range (IQR). Also, relevant graphics will be used when possible. 

When appropriate, data will be analyzed using parametric (Student’s *t*-test) and non-parametric tests (Mann–Whitney–Wilcoxon). In addition, for statistical hypothesis testing, Student’s *t*-test will be applied in case of continuous variables, while categorical variables will be compared using the chi-square test. Missing data will be handled using a multiple imputation approach.

Odds ratio (OR), corresponding 95% confidence intervals, and p-values will be calculated for each variable related to investigated outcomes. A *p*-value < 0.05 will be considered statistically significant. Univariate logistic regression models will reveal statistically significant variables associated with pre-specified outcomes. Afterward, variables documented as statistically significant in univariate logistic regression models will be included in multivariate analysis. Moreover, the prediction accuracy of time and frequency domain HRV parameters for primary and secondary outcomes will be evaluated using the Receiver Operator Characteristics (ROC) curve. The sensibility, specificity, and c-statistic of individual HRV parameters will be calculated. Additionally, the Kaplan–Meier survival curve will be used to analyze time to event variables.

In addition, the role of HRV parameters for adverse outcomes prediction will be analyzed in three subgroups of high-risk patients, including patients with chronic kidney disease, diabetes mellitus, and elderly participants.

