### 2.4. Collected Data

The following data will be collected and analyzed:Demographic data (age, sex);Time to primary PCI in relation to chest pain onset;Comorbidities (arterial hypertension, diabetes mellitus, chronic kidney disease, ischemic heart disease, stroke);Cardiovascular risk factors (advanced age, gender, high body mass index, smoking, sedentarism, inflammation);Cardiac rhythm; HRV parameters (time domain, frequency domain, and nonlinear measurements),Biological data (creatine kinase-MB—CK-MB, lactate dehydrogenase—LDH, aspartate transaminase—AST, cardiac-specific troponin, complete blood count, hemoglobin, hematocrit, glycemia, lipid profile, serum urea, and creatinine, estimated glomerular filtration rate using CKD-EPI equation, serum potassium, and sodium, C-reactive protein, N-terminal pro-b-type natriuretic peptide);Left ventricular ejection fraction (LVEF) evaluated at admission, pre-discharge, and during follow-up;Thrombolysis in myocardial infarction (TIMI) flow before and after primary PCI;Type of stent used for primary PCI;GRACE score;SYNTAX score II will be documented if three-vessel coronary disease or left main stem disease.

All data, including patients’ names and the aforementioned data, will be stored in an electronic database available only for study investigators. Collected data in relation to specific timeframes were displayed in Table 1.

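### Logistic regression is the only regression named for all outcomes, so no named analysis gives a baseline-adjusted association of continuous HRV with follow-up LVEF

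*Protocol article*

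**What the plan says.** The regression strategy is in section 2.7 of the protocol article. It says: "Univariate logistic regression models will reveal statistically significant variables associated with pre-specified outcomes". The effect measure follows the same model: "Odds ratio (OR), corresponding 95% confidence intervals, and p-values will be calculated for each variable related to investigated outcomes". The multivariable step is fed from that screen: "variables documented as statistically significant in univariate logistic regression models will be included in multivariate analysis", at a p-value threshold of 0.05. ROC curves for the time and frequency domain HRV parameters are planned for primary and secondary outcomes alike.

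Three other tools appear in section 2.7. Student's t-test is named for continuous variables, the Mann–Whitney–Wilcoxon test for non-parametric comparisons, and one sentence covers event times: "Additionally, the Kaplan–Meier survival curve will be used to analyze time to event variables". No linear, covariance-adjusted, mixed or hazard regression is named.

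Among the outcomes to which this applies, section 2.5 lists as secondary outcome (h) "LVEF and left ventricular diastolic function". It gives no cut-point for either. Section 2.4 says LVEF is "evaluated at admission, pre-discharge, and during follow-up", and Table 1 schedules echocardiography at baseline, in hospital, at 1 month and at 12 months. Section 3 promises to report the independent value of HRV for predicting primary and secondary outcomes.

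**The concern.** Logistic regression and ROC analysis both need a binary outcome. Applied to LVEF as section 2.7 is written, they require a threshold that the article does not give, so one could be chosen after the data are seen. Dichotomising also discards information on an outcome that every surviving patient with an echocardiogram contributes to.

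The second issue is the starting value. HRV is recorded around the primary PCI and LVEF is measured at admission. If patients with low HRV tend to present with low LVEF, HRV will be associated with LVEF at 12 months even if it adds nothing to the admission echocardiogram. The promised independent value cannot be claimed for LVEF unless admission LVEF is in the model, and nothing in section 2.7 ensures that it is.

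**Working it through.** The article states no power, effect size, standard deviation or event rate, so there is no figure of its own to reproduce. From the documents come N = 200 and alpha = 0.05 (two-sided assumed). Everything else below is an assumption used to size the loss.

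**1. What the named tools can deliver for follow-up LVEF**

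| Tool in section 2.7 | Continuous LVEF kept? | Continuous HRV kept? | Can adjust for admission LVEF? |
|---|---|---|---|
| Logistic regression | No | Yes | Yes, but only if it passes the univariate screen |
| ROC curve | No | Yes | No |
| t-test, Mann–Whitney | Only if HRV is split | Only if LVEF is split | No |

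No row keeps both variables continuous and adjusts for the starting value.

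**2. Loss from dichotomising LVEF**

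For a normal outcome cut at percentile p, with c the corresponding normal quantile and φ the normal density, the relative efficiency for small effects is φ(c)²/[p(1−p)].

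- p = 0.50: 0.3989²/0.25 = 0.637
- p = 0.30: 0.3477²/0.21 = 0.576
- p = 0.20: 0.2800²/0.16 = 0.490

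The loss is therefore about 36% to 51%. In patients, 200 × 0.637 ≈ 127 and 200 × 0.490 = 98.

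**3. The same loss as power**

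The correlation of HRV with LVEF that gives 80% power by linear regression at N = 200 is tanh[(1.960 + 0.842)/√197] = tanh(0.1996) = 0.197. At that correlation, 2,000 simulated studies per cut-point gave:

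| LVEF cut (percentile) | Linear regression | Logistic regression |
|---|---|---|
| 50th | 80.8% | 61.6% |
| 30th | 80.7% | 57.2% |
| 20th | 79.5% | 49.3% |

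**4. How far the starting value alone can produce an association**

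Suppose HRV is related to follow-up LVEF only through admission LVEF. The unadjusted correlation is then the product of two correlations: HRV with admission LVEF, and admission with follow-up LVEF. With an assumed 0.3 for the first and 0.5 to 0.7 for the second, it is 0.3 × 0.5 = 0.15 to 0.3 × 0.7 = 0.21. The upper value exceeds the 0.197 that N = 200 detects with 80% power. A nominally significant finding could therefore arise with no independent contribution from HRV.

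**5. Clinical events: logistic against Cox**

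Simulations (1,000 per scenario) used N = 200, an assumed hazard ratio of 1.6 per SD of HRV, 1-year event rates of 5% to 40% and dropout of 0% to 20%. The power difference was at most about 2 points. At a 10% event rate without dropout, Cox had 57.9% and logistic 56.8%. At a 20% event rate with 20% dropout, Cox had 83.9%; logistic had 82.4% counting losses as event-free and 81.7% on complete cases. Logistic regression costs little for events read at a fixed horizon.

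**The case against.** The best defence is that section 2.7 is condensed and speaks generally. It names the t-test and Mann–Whitney for continuous data. Admission LVEF is a collected variable that could pass the screen into the multivariable step, whose model type is not separately stated. No LVEF cut-point appears anywhere, so dichotomisation is inferred. Outcome-by-outcome models are often left to the full protocol or analysis plan.

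Part of this stands: admission LVEF is not excluded, and the plan does not say outright that LVEF will be split. But the article ties odds ratios and logistic screening to its outcomes without exempting (h). The group tests cannot give an adjusted estimate, and entry by a significance screen does not guarantee baseline adjustment. The point rests on the model that is named.

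Several stronger readings are tempting, but the documents do not support them:

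- **Change in LVEF is confounded with its starting value.** No change-in-LVEF analysis is defined. Section 2.5 lists LVEF as an outcome at set times, and recovery is mentioned only in the Discussion.
- **Events are badly served by logistic regression.** Section 2.5 evaluates outcomes in hospital, at 1 month and at 1 year, where logistic regression is adequate and the simulated power loss is negligible. Kaplan–Meier is also named for event times.
- **Competing deaths will bias the risk curves.** The article does not say which variables get Kaplan–Meier curves, or that one minus Kaplan–Meier will be reported for non-fatal events. The primary composite counts all deaths.
- **Baseline adjustment is worth 1.33 to 1.96 times the patients.** That is 1/(1−r²) at assumed r = 0.5 to 0.7, and it requires HRV to be uncorrelated with admission LVEF. With a correlation of 0.3, the factor 1 − 0.3² = 0.91 reduces it to 1.33 × 0.91 = 1.21 and 1.96 × 0.91 = 1.78. The quantity estimated also changes. Adjustment is needed here for interpretation; no particular precision gain can be promised.

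**Conclusion.** The point holds for secondary outcome (h). Logistic regression is the only regression named, it is applied to all pre-specified outcomes, and no named analysis yields a baseline-adjusted association between continuous HRV and follow-up LVEF. If LVEF is dichotomised to fit the named model, about 36% to 51% of the information is lost, and 80% power becomes roughly 62% to 49%. These figures assume a normal outcome and cuts between the 50th and 20th percentiles; neither comes from the article. Independently of power, an unadjusted association may only reflect LVEF at presentation. The primary composite and the other binary events are not materially affected.

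**What to change.** In section 2.7, or in the analysis plan, separate continuous from binary outcomes:

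- **LVEF:** linear regression of the follow-up value on the HRV parameter kept continuous, with admission LVEF as a forced covariate that does not depend on the univariate screen, in patients alive at that visit.
- **Diastolic function:** the same model for whichever ratio is available, since section 2.5 guarantees only one of E/A and E/e prime, with its admission value as covariate.
- **In-hospital and fixed-horizon binary events:** keep logistic regression.
- **Optional:** a Cox model for time to the 1-year primary composite, if event dates are recorded. Section 2.4 does not list them, and Table 1 shows outcomes by visit. Its merit is adjusted estimates with censoring of incomplete follow-up; little power gain should be expected.

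The cost is a few sentences and standard software, with no added patients or visits. One small downside should be stated: analysing LVEF in survivors conditions on survival, which HRV may itself predict. The text should also say that the planned multiple imputation does not create LVEF values after death.
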